#### Control

All women randomized to the control arm will receive standard antenatal care. In addition, health workers will visit the women every two months starting from 20 weeks of gestation to measure their weight using a digital weighing scale. If any woman is gaining weight outside of the applicable US Institute of Medicine recommended range, she will be advised to visit Matlab hospital (icddr,b) or a government health facility immediately for further evaluation and management. If the condition demands, our health workers will ensure that an appropriate referral is made to a tertiary health care facility.

Health workers will counsel all participants, both in the intervention and in the control group, to make at least four antenatal visits. All women will be provided with general education to maintain a balanced diet and to remain physically active during pregnancy.

#### Participant Enrollment and Follow-up

In Matlab, pregnancies are usually diagnosed by 12 weeks of gestation and recorded by Health and Demographic Surveillance System field staff. We will obtain this information from Health and Demographic Surveillance System and conduct baseline interviews to identify eligible participants for this study. Health worker will continue to conduct baseline interviews and enroll participants whenever newly pregnant women are identified, and to obtain information from the Health and Demographic Surveillance System until the desired sample size is met. Each potential participant will be provided with a consent form in the local language (Bengali). Health worker will also explain the study in detail and answer any questions. If a woman agrees to participate in the study, her signature or left thumb impression and that of a witness will be taken. A health worker will also sign the consent form in front of the woman and the witness on behalf of the principal investigator of the study. Then the health worker will conduct a short interview using a semistructured questionnaire and record the woman’s height and weight. If eligibility criteria are satisfied, the health worker will open the sealed envelope (in sequence and in front of the participant and the witness) that assigns the participant to the allocated group (intervention or control). If the woman does not meet the eligibility criteria, she will be informed that she cannot take part in the study.

Once enrolled, the women will be followed from 20 weeks of pregnancy until delivery. Health worker will visit women in the intervention arm weekly and those in the control arm every two months. Furthermore, health workers will maintain mobile communication with all women to keep track of the progress of the pregnancy. Health worker will collect outcome data from the households and health facilities by follow-up visit or by phone.

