#### Blinding

Neither the participants nor the investigators and assessors of outcomes can be blinded to allocation because of the nature of service delivery that will be provided, and thus, we are obliged to make the randomized controlled trial nonblinded; however, it should be mentioned that the outcomes of the trial are objective in nature, therefore, the risk of bias is minimal. Furthermore, the randomization, as well as statistical analysis, will be carried out by someone unconnected to the enrollment process.

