##### Acceptability

The acceptability of using Health Gauge for continuous self-monitoring of blood pressure will be evaluated by women in the intervention group using a 5-point Likert scale. In addition, interviews will be conducted to assess the women’s perception two times: during the third trimester and after delivery.

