#### Training of the Health Workers Delivering the Intervention

Four skilled and experienced health workers who each have at least 12 years of formal education will undergo a fifteen-day intensive training program, which will include lectures, mock interviews, role play, and field practice at the community level. A training manual will be developed to guide the health workers in the field.

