#### Outcome Measures

##### Primary

The feasibility outcomes (primary outcomes) will be recruitment rate, retention rate, adherence to the protocol, and acceptability. Recruitment rate will be defined as the mean number of participants recruited per month. Both eligibility and consent rate will be recorded. Recruitment rate is an important outcome because unforeseen enrolment challenges may arise and are crucial to identify in a pilot study. Retention rate will be defined as the proportion of participants who will participate in the full follow-up period of the study (from 20 weeks of gestation until delivery). Adherence will be defined as the proportion of participants following the intervention protocol. There may be several reasons why a participant does not follow the intervention protocol properly. Health workers will note the cause and the number of instances of nonadherence in a log sheet. Nonadherence will be classified into protocol deviations caused by circumstances beyond their control and those that are not (for example, the participant chose to remove Health Gauge). Participant will rate the acceptability of using Health Gauge for continuous self-monitoring of blood pressure two times during the follow-up period using a 5-point Likert scale. Acceptability will be evaluated once during the third trimester and again after delivery.

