A major limitation of this study is that pregnant women without access to electricity at home or who are not familiar with smartphones must be excluded. Additionally, limited internet access to the internet among participants as a result of Matlab’s rural setting makes live monitoring of blood pressure data difficult. Access to the blood pressure data will only be available at weekly intervals when the health workers visit the participants and synchronize the data with the online server. Nevertheless, pregnant women will be trained to take their own blood pressure measurements using Health Gauge. They will be informed to contact the health workers by phone and visit the nearest health facility if they find that their blood pressure is greater than or equal to 140/90 mmHg on two consecutive measurements. Another limitation is the lack of nonsubjective qualitative approach to ascertain acceptability and usefulness of the intervention. Finally, the small sample size limits the statistical power to detect any effect of the intervention on clinical outcomes; however, the sample size should be sufficient to accomplish the objectives of this pilot trial.

After successful completion of this study, the data will be accumulated, analyzed, and reported. The companion app for Health Gauge will be evaluated and improved using data generated in the study and machine learning for more accurate and precise blood pressure measurements; the design of Health Gauge may also be modified or adapted, if necessary. In the definitive trial, the intervention may include additional educational materials and focused counseling sessions. The implementation protocol may be revised to allow women to self-monitor weight gain akin to the protocol used for blood pressure measurements. Based on the results of and experience gained from this pilot trial, we will design a full-scale randomized controlled trial to test the efficacy of the intervention.

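### The Blinding section calls the trial's outcomes objective and the bias risk minimal, which is wrong for acceptability: a subjective primary outcome, at risk of courtesy bias if delivering staff collect it

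*Protocol article*

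**What the plan says.** All references are to the protocol article.

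- **Blinding.** Participants, investigators and outcome assessors are all unblinded. The section then reassures the reader that "the outcomes of the trial are objective in nature, therefore, the risk of bias is minimal". No outcome is excepted. Only randomization and statistical analysis are kept separate from enrollment.
- **Outcome Measures, Primary.** "The feasibility outcomes (primary outcomes) will be recruitment rate, retention rate, adherence to the protocol, and acceptability". On the last of these, "Participant will rate the acceptability of using Health Gauge for continuous self-monitoring of blood pressure two times", once in the third trimester and once after delivery.
- **Acceptability.** Use of the device "will be evaluated by women in the intervention group using a 5-point Likert scale". Interviews on the women's perceptions are added at the same two times. The section does not say who takes the rating or holds the interviews.
- **Participant Enrollment and Follow-up.** "Health worker will collect outcome data from the households and health facilities by follow-up visit or by phone". Health workers also obtain consent, open the allocation envelope and visit intervention women weekly.
- **Intervention**, and the section headed "Training of the Health Workers Delivering the Intervention". Health workers synchronize the device data each week and weigh the women each month. Four of them are trained, and the training includes mock interviews.
- **Discussion.** "Another limitation is the lack of nonsubjective qualitative approach to ascertain acceptability and usefulness of the intervention".

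**The concern.** The protocol sets bias aside on the ground that outcomes are objective, but one of its four primary outcomes is an opinion. A woman who gives that opinion to someone who has visited her every week, and whose work is to support the device, may soften a poor rating out of politeness.

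Only the intervention arm rates, so no control rating exists against which a shift would show. The Discussion expects the pilot's findings on acceptability to inform the definitive trial and changes to the device and app. A rating that is too favourable would feed into those decisions with no warning attached, because the Blinding section tells the reader that bias is minimal.

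**Working it through.** The protocol gives no expected acceptability, threshold or bias estimate, so there is no figure to reproduce. The check is mainly a comparison of sections.

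**1. Is the objectivity statement true of every primary outcome?** The Blinding section speaks of the trial's outcomes without exception. The Primary section lists acceptability among them and defines it as a participant's rating. The Acceptability section adds interviews on perception. The Discussion lists the lack of a nonsubjective approach as a limitation. The first statement cannot stand beside the other three, so it fails for one primary outcome in four.

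**2. Who collects the rating?** The Acceptability section is silent. The general sentence in Participant Enrollment and Follow-up assigns outcome data to health workers and does not except acceptability. The article describes one trained team of four, under a heading that says they deliver the intervention, and describes no separate interviewer. Collection by the delivering team is thus a strong inference, but it is not stated.

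**3. Is there a safeguard for this outcome?** The Data Quality section lists re-interview and back-checking in general terms. It does not say that these are independent or that they cover acceptability.

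**4. How large could the effect be?** This is an illustration only. Let *p* be the true proportion of women who find the device acceptable, and *s* the proportion of the others who answer favourably out of courtesy. Neither value is in the documents.

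Observed = *p* + (1 − *p*) × *s*

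| Assumed *p* | *s* = 10% | *s* = 25% | *s* = 50% |
|---|---|---|---|
| 60% | 64% | 70% | 80% |
| 80% | 82% | 85% | 90% |

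The shift is (1 − *p*) × *s*. It runs from 0.20 × 0.10 = 2 points to 0.40 × 0.50 = 20 points.

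The exact 95% confidence interval for 24 of 35 (69%) is 51% to 83%. An interval describes sampling error around whatever was recorded, so it would not reveal a shift of this kind.

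**5. What would this do to the planned summary?** The Data Analysis section plans median and interquartile range for ordinal variables, not a percentage. Suppose that a rating of 4 or 5 counts as favourable (an assumption, as the article sets no cut-off) and that 35 women rate.

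- The median is the 18th ordered rating, (35 + 1)/2. The lower quartile is about the 9th, (35 + 1)/4.
- With 21 women (60%) truly favourable, 14 are below the line. The 18th rating is already favourable and the 9th is not.
- At *s* = 25%, 3 or 4 women move up and 10 or 11 stay below. The 9th rating is still unfavourable.
- At *s* = 50%, 7 women move up and 7 stay below. The 9th rating becomes favourable.

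In this example the median stays in the favourable range throughout, while the lower quartile crosses the line only at the upper end of the assumed range. The effect on the planned summary may therefore be nil, or may be to hide the dissatisfied group.

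**The case against.** Several points on the other side have weight.

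- **The collector is not named.** The general sentence on outcome data may be meant mainly for perinatal and clinical outcomes. The wording that participants rate the device is also compatible with self-completion. A condensed article may leave such detail to the full protocol. This stands: the missing name is not itself an error, and a reader who infers that the article states collection by the delivering workers goes beyond the text.
- **Direction and size are not shown.** A reader might also infer that acceptability will be overstated, or that bias can act only in the favourable direction. Nothing in the documents establishes either. Upward is the most plausible direction, and no more can be said.
- **The Blinding section concerns knowledge of allocation.** Acceptability is rated in one arm, so blinding could not have protected it and no between-arm contrast is distorted. This narrows the point to a single-arm descriptive estimate. It does not rescue the sentence, which covers the trial's outcomes without limit.
- **The Discussion already discloses subjectivity.** It does so, but it leaves the claim of minimal bias in place and does not address who takes the rating.
- **It may be late.** The Results section reports enrollment complete as of September 2019 and follow-up expected to end by the end of October 2019. Many ratings may already have been taken. This limits what can change in data collection, but not in the text or the reporting.

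**Conclusion.** The point holds in a limited form. The statement that outcomes are objective and bias minimal is wrong for acceptability, and the protocol's own sections show it. This part rests on no assumption.

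The risk of courtesy bias rests on the inference that the named outcome collectors also take the ratings, with no safeguard specific to this outcome described. That makes acceptability an outcome at risk of upward bias, not one shown to be overstated. The size cannot be derived from the documents. The 2 to 20 points hold only for the assumed values of *p* and *s*, and they concern a percentage that the plan does not specify. The 35 raters are the full arm. With the 20% attrition allowed for in the Sample Size section, 35 × 0.80 = 28 might remain for the rating after delivery.

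**What to change.** 1. In the Blinding section, limit the objectivity statement to the outcomes that are objective, and acknowledge the risk of bias for acceptability.
2. State who takes the ratings and interviews.
3. For all ratings still outstanding, either have the woman mark the 5-point rating herself and seal it, or have it taken by an existing staff member who does not deliver the intervention to that woman. Apply the second option to the interviews. A swap among the four health workers would do this without extra staff, although it keeps the interviewer within the delivery team and so removes the pressure only in part.
4. Where the delivering worker took a rating, report this and interpret acceptability accordingly.

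Items 1, 2 and 4 are text and reporting changes. Item 3 costs minor logistics for at most two short contacts with each of at most 35 women, and women who cannot read will need help with a self-marked form. The ratings may turn out less favourable.

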#### Data Collection

##### Questionnaire Preparation

Questionnaires will be prepared in English, and then translated into Bengali with back-translation. The Bengali questionnaires will be used in the field. Pretesting will be done before finalizing the questionnaire. Field staff will be given training on administering the questionnaires.

##### Baseline Questionnaire

A brief questionnaire will be designed to collect baseline information on the participants. Questions on age, education level, occupation, and work status of the pregnant woman, her husband, and members in her household will be included. Information on household income, marital status, parity, whether pregnancy was intended, living conditions, tobacco use, health and nutrition, knowledge of nutrition and dietary practices, health-seeking behavior, and media exposure will also be collected.

##### Follow-up Questionnaire

Health worker will administer a follow-up questionnaire weekly to the women in the intervention group to collect information on signs and symptoms associated with hypertensive disorders and complications, including sense of awareness, headache, blurring of vision, abdominal pain, nausea and vomiting, edema, and convulsions over the previous week.

##### Acceptability

The acceptability of using Health Gauge for continuous self-monitoring of blood pressure will be evaluated by women in the intervention group using a 5-point Likert scale. In addition, interviews will be conducted to assess the women’s perception two times: during the third trimester and after delivery.

##### Perinatal Outcomes

Information including predelivery weight, perinatal outcomes, and infant length, weight, and head circumference at birth will be obtained from hospital records, discharge certificates given after institutional delivery or from the woman herself using a simple checklist.

##### Health and Demographic Surveillance System Records

Age and asset score (wealth quintile) of the study participants will be retrieved from the Health and Demographic Surveillance System database.

##### Anthropometry

Health worker will measure the height and weight of each pregnant women following standard anthropometric procedures. Height will be measured using locally made standardized stadiometer. Weight will be measured using a digital weighing scale.

#### Training of the Health Workers Delivering the Intervention

Four skilled and experienced health workers who each have at least 12 years of formal education will undergo a fifteen-day intensive training program, which will include lectures, mock interviews, role play, and field practice at the community level. A training manual will be developed to guide the health workers in the field.

#### Data Quality

To ensure the accuracy of the data, several quality control measures will be undertaken at different stages of the data collection procedure: (1) Since the participants are women, we will recruit experienced female health workers for data collection to minimize observer bias. (2) We will establish a multilayered monitoring system to maintain and standardize data quality. A health research supervisor will check data consistency daily by thoroughly checking the filled-out questionnaires at the end of the day. (3) We will perform spot-checking, re-interview, back-checking, and provide necessary feedback. (4) Regular meetings with the research team and refresher training sessions (if required) will be arranged for the health workers.

#### Outcome Measures

##### Primary

The feasibility outcomes (primary outcomes) will be recruitment rate, retention rate, adherence to the protocol, and acceptability. Recruitment rate will be defined as the mean number of participants recruited per month. Both eligibility and consent rate will be recorded. Recruitment rate is an important outcome because unforeseen enrolment challenges may arise and are crucial to identify in a pilot study. Retention rate will be defined as the proportion of participants who will participate in the full follow-up period of the study (from 20 weeks of gestation until delivery). Adherence will be defined as the proportion of participants following the intervention protocol. There may be several reasons why a participant does not follow the intervention protocol properly. Health workers will note the cause and the number of instances of nonadherence in a log sheet. Nonadherence will be classified into protocol deviations caused by circumstances beyond their control and those that are not (for example, the participant chose to remove Health Gauge). Participant will rate the acceptability of using Health Gauge for continuous self-monitoring of blood pressure two times during the follow-up period using a 5-point Likert scale. Acceptability will be evaluated once during the third trimester and again after delivery.

##### Secondary

Clinical outcomes will be rate of weight gain during pregnancy; infant weight, length, and head circumference at birth; hypertension status; adverse consequences of hypertensive disorders; blood pressure profile and heart rate; risk factors; and serious adverse events. Rate of weight gain during pregnancy will be measured in kilograms per week and be calculated by subtracting the baseline (enrollment) weight from the predelivery weight and dividing that value by the number of weeks between the two time points. Infant weight will be measured in grams, infant length will be measured in centimeters, and head circumference at birth will be measured in centimeters. The number of women with chronic hypertension and who develop hypertensive disorders will be recorded. Adverse consequences of hypertensive disorders of pregnancy will be defined as maternal or fetal complications or consequences that arise in a woman with chronic hypertension or in a previously normotensive woman who has developed some form of hypertensive disorder after at least 7 days of intervention. Maternal complications are abruptio placentae, disseminated coagulopathy or hemolysis, elevated liver enzymes and low platelets syndrome, pulmonary edema, acute kidney injury, eclampsia, liver failure or hemorrhage, stroke, or death. Fetal or neonatal complications are intrauterine death or stillbirth, preterm birth, small for gestational age, low birth weight, hypoxic brain injury, and complications associated with small for gestational age, low birth weight, or prematurity. Episodes, type, and timing of occurrence of adverse consequences will be reported. The blood pressure profile along with heart rate from 20 weeks of pregnancy until delivery will be recorded. The prevalence of specific risk factors along with the sociodemographic profile of the participants will be determined. We do not anticipate any serious adverse events in this trial; however, should any other adverse events arise they will be reported in detail.

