#### Study Population Eligibility Criteria

Inclusion criteria are pregnant women in Matlab, Bangladesh with a high-risk pregnancy who are between 12 and 16 weeks of gestation and are between 15 and 50 years of age. Exclusion criteria are women who have a congenital malformation or anomaly, a chromosomal abnormality (such as Down syndrome), chronic debilitating illness, diagnosed psychosis, no electricity at home, and never used a smartphone. In this study, a high-risk pregnancy is defined to identify women at risk of developing hypertensive disorders of pregnancy or their complications [3], as a pregnant woman who meets any one or more of the following criteria: had preeclampsia or gestational hypertension in a previous pregnancy, has chronic hypertension, has chronic kidney disease, had pregestational diabetes, has systemic lupus erythematosus or antiphospholipid syndrome, pregnancy is her first pregnancy (nulliparity), is aged 40 years or older, interpregnancy interval is less than 2 years or greater than 10 years, has a BMI of 35 kg/m^2^ or more, has polycystic ovary syndrome, has a family history of preeclampsia, pregnancy is a multiple pregnancy, has pre-existing thrombophilia, used of selective serotonin reuptake inhibitors beyond the first trimester, has donated a kidney, underwent in vitro fertilization, and has a family history of coronary heart disease.

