#### Intervention

Before 20 weeks of gestation, each woman in the intervention arm will be provided with a Health Gauge device and with a smartphone, if she does not already have one. The app for Health Gauge will be installed on each participant’s smartphone. The women will be asked to use the Health Gauge device and app to measure their blood pressure at least two times a day (morning and evening), starting from 20 weeks of gestation. The blood pressure measurement records will be automatically stored in the smartphone app. Participants will be trained to charge and operate the Health Gauge device. Most women in rural Matlab do not have internet access. Hence, trained health workers will visit the women weekly and synchronize the smartphones with tablet computers to collect the stored data and to upload the data to an online server. The health workers will also measure the weight of the participant using a digital weighing scale every month. If any woman is found to be hypertensive (blood pressure is greater than or equal to 140/90 mmHg on two consecutive measurements), is presenting signs and symptoms associated with hypertensive disorders or associated complications (described later), or is gaining weight outside of the applicable US Institute of Medicine recommended range [11], she will be advised to visit Matlab hospital (icddr,b) or a government health facility immediately for further evaluation and management. If the condition demands, our health worker will ensure that an appropriate referral is made to a tertiary health care facility. This intervention will be in addition to the conventional programs offered by icddr,b as well as government health facilities.

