#### Data Analysis

Data presentation, analysis, and reporting will be carried out according to CONSORT randomized pilot and feasibility trial guidelines [20]. The feasibility outcomes will be reported descriptively as well as narratively. Only descriptive statistics will be reported for the clinical outcomes. Mean and 95% confidence interval will be reported for continuous variables, median and interquartile range will be reported for ordinal variables, and raw count (number and percentage) will be reported for categorical variables. No conventional test of hypothesis will be performed since as a pilot trial, statistical power is lacking; however, the estimates of effect using clinical outcomes as they are likely to be measured in the definitive trial will be reported as estimates with 95% confidence interval. Analyses will be performed at the end of the study. No interim analyses or subgroup analyses are planned due to the short duration and small sample size of this pilot trial. Data will be analyzed using Stata software (version 14.1; StataCorp LLC).

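### New-onset hypertension enters the adverse-consequences outcome through a time condition with no control-arm equivalent and a diagnosis sought unequally by arm, so the planned between-arm estimate is biased

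*Protocol article*

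**What the plan says.** All references are to the protocol article.

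- **Definition.** Under Outcome Measures, Secondary, adverse consequences are "maternal or fetal complications or consequences that arise in a woman with chronic hypertension or in a previously normotensive woman", the latter qualified as "in a previously normotensive woman who has developed some form of hypertensive disorder after at least 7 days of intervention". There are two routes in: chronic hypertension, or new-onset disorder subject to the seven-day condition.
- **Eligibility.** Chronic hypertension is among the high-risk criteria ("has chronic hypertension, has chronic kidney disease"), so the first route is open in both arms.
- **Intervention arm.** Women are asked to "measure their blood pressure at least two times a day (morning and evening), starting from 20 weeks of gestation". Health workers visit weekly, and the Follow-up Questionnaire section gives a weekly symptom questionnaire to this arm only.
- **Control arm.** "All women randomized to the control arm will receive standard antenatal care", and in addition "health workers will visit the women every two months starting from 20 weeks of gestation to measure their weight". No study blood pressure measurement is described for this arm.
- **Use of the outcome.** Data Analysis limits clinical outcomes to descriptive statistics without hypothesis tests, but also promises "the estimates of effect using clinical outcomes as they are likely to be measured in the definitive trial", with 95% confidence intervals.
- **Data source.** "Information including predelivery weight, perinatal outcomes, and infant length, weight, and head circumference at birth will be obtained" from hospital records, discharge certificates or the woman herself. Neither that section nor Participant Enrollment and Follow-up restricts outcome collection by arm or by hypertension diagnosis.

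**The concern.** An outcome compared between randomised arms should have the same entry rule and the same chance of being recorded in each. For new-onset disorder this one has neither.

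First, the clock is time on the intervention, and control women do not receive it. Second, whether a previously normotensive woman enters depends on a hypertension diagnosis made after allocation, and earlier diagnosis is the mechanism by which the intervention is meant to work. The Background itself says standard antenatal care often delays or misses these disorders. A stillbirth, preterm birth or small-for-gestational-age birth after unrecognised hypertension may go uncounted, and this would happen mostly in the control arm.

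At stake is what the pilot hands on. Its stated aim is to test the design and methods of the definitive trial. A definition that adds events to the arm with better detection could make a useful intervention look harmful, and could be carried into the larger trial.

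**Working it through.** The article states no event rate, effect size or power for this outcome, so there is no plan figure to reproduce. The check compares the two readings of the text and then illustrates the size under assumptions.

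**Inputs from the article:** 35 women per arm (Sample Size). Hypertensive disorders complicate 10% of all pregnancies (Background), used only as the lower anchor for new-onset disorder because no rate is given for this high-risk group.

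**Assumptions (not in the article):** no true effect; chronic hypertension c = 0 to 5%; new-onset disorder n = 10 to 30%; complication risk r = 30 to 50% among hypertensive women; detection of new-onset disorder d (intervention v control) of 100% v 80%, 100% v 60% or 90% v 50%. Chronic hypertension is taken as known in both arms, because the Background defines it as present or detected before 20 weeks and device readings start at 20 weeks. Detection is taken as unrelated to whether a complication follows.

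**Reading 1, literal.** Control women count only through chronic hypertension.
- Control: 35 × c × r runs from 0 to 35 × 0.05 × 0.50 = 0.875, so 0 to 0.9 expected cases.
- Intervention, full detection: 35 × (c + n) × r runs from 35 × 0.10 × 0.30 = 1.05 to 35 × 0.35 × 0.50 = 6.125, so 1.1 to 6.1 expected cases.

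**Reading 2, the condition taken as time in follow-up from 20 weeks.** The expected proportion counted is (c + n × d) × r, so r cancels:

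Apparent risk ratio = (c + n × d_intervention) / (c + n × d_control)

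| c | n | Detection | Calculation | Ratio |
|---|---|---|---|---|
| 5% | 10% | 100% v 80% | 0.150 / 0.130 | 1.15 |
| 2% | 20% | 100% v 80% | 0.220 / 0.180 | 1.22 |
| 2% | 20% | 100% v 60% | 0.220 / 0.140 | 1.57 |
| 2% | 20% | 90% v 50% | 0.200 / 0.120 | 1.67 |
| 0% | 10–30% | 90% v 50% | 0.90 / 0.50 | 1.80 |

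The first and last rows are the extremes over the whole grid: about 1.15 to 1.80, where the true ratio is 1.

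**In events.** The excess in the intervention arm is 35 × n × (d_intervention − d_control) × r. It runs from 35 × 0.10 × 0.20 × 0.30 = 0.21 to 35 × 0.30 × 0.40 × 0.50 = 2.1 events.

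**All randomised women counted from a common start.** The detection terms drop out, and with no true effect the expected ratio is 1 whatever the detection rates.

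**The case against.** The case for leaving the definition alone has several parts.

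- **The definition is an either/or.** A reader might infer that no control woman can ever contribute. The text does not support that: the seven-day condition naturally attaches only to new-onset disorder, and control women with chronic hypertension qualify. This stands, and it limits the defect to the new-onset route.
- **The literal reading is strained.** Follow-up in both arms starts at 20 weeks, so the phrase may mean the intervention period, and a condensed article may leave the control-arm start to the full protocol. That is fair. A reader might also infer that the arms cannot be compared at all; on this softer reading they can, but with bias. The softer reading does not remove the unequal search for the diagnosis.
- **The text speaks of a disorder developing, not being detected.** True, and some events, such as eclampsia, reveal the disorder themselves, which would shrink the bias. Stillbirth, preterm birth and small-for-gestational-age birth need not, and a disorder nobody measured cannot be recorded.
- **It is a secondary outcome of a feasibility pilot.** This stands. The primary outcomes are recruitment, retention, adherence and acceptability. Infant weight, length and head circumference are recorded without the condition. At about 0.2 to 2 extra events per arm, a confidence interval would swamp the bias in this dataset.
- **Larger ratios.** Ratios above 2 can be produced by assuming false hypertensive labels in the intervention arm or by applying unequal detection to chronic hypertension as well. The article gives no false-label rate, and its definition of chronic hypertension argues against the second step.

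The Blinding section's argument that objective outcomes keep bias minimal does not answer the point. The events may be objective, but the rule that admits them is not applied equally.

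**Conclusion.** The definition is wrong as written for previously normotensive women. Its time condition cannot be applied in the control arm, and repairing the clock alone leaves entry dependent on a diagnosis sought far more intensively in the intervention arm. The planned estimate is biased, probably against the intervention, by an apparent risk ratio of about 1.15 to 1.80 under no true effect. That range rests wholly on the assumed detection, prevalence and independence stated above; the direction rests on the article's own account of the two arms.

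Severity is moderate. No primary outcome, sample size or power figure is affected. The harm lies in passing this definition, and an estimate based on it, to the definitive trial.

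**What to change.** In the secondary outcome definition:

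1. Replace the seven-day condition with a start point common to both arms, for example 20 weeks of gestation or time since randomisation.
2. Base any between-arm estimate on the listed maternal and fetal or neonatal complications in all randomised women, whatever their hypertension diagnosis.
3. Keep the count among women with chronic or new-onset hypertension as a descriptive breakdown by arm, without an effect estimate.

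**Cost.** This changes wording and tabulation. The article's outcome collection is not restricted by arm or diagnosis. It reports follow-up as ongoing and analysis as still to come, so on its timeline the change could be documented before analysis.

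**Downside.** The all-women outcome is less specific to hypertension. At the national figures in the Background, 35 × 0.305 = 10.7 births per arm would be small for gestational age and 35 × 0.141 = 4.9 preterm, with overlap between the two, so events unrelated to hypertension could dominate. Reporting the components separately, beside the descriptive hypertension breakdown, keeps that visible.
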